#### Participant measures

At baseline, we will collect data on name, postcode, NHS number, email address, telephone number, date of birth, gender, marital status, employment, education, menopausal status, year of diagnosis, stage of cancer at diagnosis, tumour type, breast cancer treatment received, comorbidities, AET regimen, supportive therapies used following AET prescription, and previous exposure to ACT, Cognitive Behavioural Therapy and mindfulness.

We will obtain participant consent to apply to NHS Digital for participant-level AET prescribing or dispensing data.

The following patient-reported measures will be used.

##### Morisky Medication Adherence Scale (MMAS-8)^82^

An eight-item, patient report measure for assessing medication adherence. It provides an overall adherence score, as well as a score for intentional and non-intentional non-adherence.

##### Voils DOSE-non-adherence measure—extent scale^83^

A three-item patient report scale to assess the extent of medication adherence.

##### European Organisation for Research and Treatment of Cancer (EORTC) QLQ-C30^84^

A 30-item, patient report tool to assess health-related quality of life in cancer patients.

##### EORTC QLQ-BR45^85^

A 45-item self-report measure for assessing quality of life in patients with breast cancer.

##### EORTC-IL133

Two items assessing vaginal discharge and abnormal vaginal bleeding, taken from the EORTC item library.

##### EQ-5D-5L^86^

A five-item, self-assessed, health-related quality of life questionnaire.

##### Multidimensional psychological flexibility inventory-short form^87^

A 24-item self-report questionnaire assessing psychological flexibility and inflexibility.

##### Beliefs about Medication Questionnaire (BMQ-AET)^88^

The BMQ-AET is a modified version of the BMQ to increase its relevance to women taking AET. It is a 10-item patient report measure which assesses specific medication beliefs.

##### Self-Report Behavioural Automaticity Index (SRBAI)^89^

A four-item self-report tool that captures habitual behaviour patterns, specifically with regard to automaticity of the behaviour.

##### Depression Anxiety Stress Scales (DASS)−21^90^

A 21-item self-report measure of negative emotional states.

##### McGill quality of life-revised^91^

A 14-item, patient-report tool designed to measure physical well-being, physical and psychological symptoms, existential well-being and support, as well as overall quality of life of people with life-threatening illness.

##### UK cancer cost questionnaire^92^

An adapted version of the UK cancer cost questionnaire. The questionnaire assesses services and medications participants have used while participating in the trial.

#### Site measures

##### Usual care assessment

Each site will record what services are offered as part of usual care.

#### Health economic assessments

##### Intervention costs

We will estimate the cost of developing each intervention component. We will use NHS Reference Costs and Personal Social Sciences Research Unit costs to estimate delivery costs for the ACT component.

#### Process evaluation measures

##### Adherence to intervention components

To assess fidelity of receipt of the intervention components, participants will be asked whether they received each of the intervention components they were randomised to, and how much of it they read. Participants who received the ACT component will additionally be asked about how much of the home practice tasks they completed, and how many of the audio files they listened to.

##### Acceptability Questionnaire (AQ)^93^

A five-item self-report measure assessing acceptability. Participants randomised to the SMS component will be asked an additional item about acceptability of the frequency of the SMS messages. Participants randomised to the ACT component will be asked an additional 15 items about the acceptability of elements of ACT sessions. Participants will be provided with an open text question about acceptability. A single item will additionally ask about overall trial acceptability.

##### Study Participant Feedback Questionnaire (SPFQ)^94^

A modified version of the SPFQ assessing participants’ experience during the trial will include two, three and two items at baseline, 2-month and 4-month follow-ups, respectively.

##### ACT Fidelity Measure (ACT-FM) (therapist subscale)^95^

A seven-item subscale from a measure of fidelity to the principles of ACT will be scored by an expert in ACT while reviewing therapy recordings. This subscale includes items measuring prescribed (four items) and proscribed (three items) therapist behaviours.

##### Procedural fidelity checklist

A checklist to assess fidelity of delivery of the ACT component recorded by the therapist at the end of each session to self-rate whether they undertook crucial intervention procedures. It includes four to eight items, depending on the session. Additional items will be used for therapists to record participant engagement with the module materials.

##### Research nurse questionnaire

A nine-item bespoke questionnaire to report RN experiences of recruiting to a fractional factorial trial. Demographic and role information will also be collected for the RNs.

### Process evaluation

#### Fidelity of design

Two independent coders will identify and record which BCTs from the BCT Taxonomy v1 are present in each intervention component.^48^

#### Fidelity of training

Each therapist’s first ACT session will be assessed for competency using the ACT-FM by a clinically trained member of the research team ([name]).

#### Fidelity of delivery

We will collect SMS receipt data, record the number of information leaflets and website details sent to participants, use independently rated competency scores on the ACT-FM therapist stance subscale and report scores on the procedural fidelity checklist.

#### Fidelity of receipt

We will use self-reported data on receipt and reading of the materials within an intervention component, SMS opt outs, website tracking data, therapist-reported attendance and engagement with ACT session and independently assessed engagement with ACT session.

#### Participant and therapist interviews

Semistructured interviews with participants will investigate the acceptability, and fidelity of receipt and enactment of the intervention components. ACT therapists will be interviewed to gain an insight into their experiences of intervention delivery, and the acceptability of the ACT component. Interviews lasting approximately 1 hour will be conducted via video conferencing software or telephone.

### Sample size

The primary objective is to estimate rates of eligibility, recruitment, retention and component adherence to inform the future trial. Allowing for 80% retention (the average across eight studies^20^), 80 participants (n=10 per condition) will be randomised. This is sufficient to inform the sample size of the optimisation trial assuming adherence data are pooled across conditions.^96^

### Patient and public involvement

A user group of five breast cancer survivors have supported the development of the intervention components and trial protocol. Two representatives are members of the trial management group.

### Independent monitoring

The Trial Steering Committee (TSC), with an independent Chair, will be responsible for trial oversight. The TSC will be provided with reports prepared by the CTRU based on an agreed TSC Charter and containing the information agreed in the trial monitoring plan. It includes an Independent Chair, at least two other independent members and two patient representatives. The Chief Investigator and other members of the TMG may attend the TSC meetings and report progress. A separate data monitoring committee was considered by the TSC to be unnecessary. The TSC will adopt a safety function.

### Data management

Data collection forms transferred to or from the CTRU will be coded with a study number (made up of the recruitment site code and the participant’s unique sequential trial number), the participant’s initials and date of birth. Study data will be held securely on paper and electronically at the University of Leeds CTRU, and appropriate processes put in place for the transfer, storage, restricted access and disposal of personal information. Relevant standard operating procedures, guidelines and work instructions in relation to data management, processing and analysis of data will be followed.

### Analysis

A detailed statistical analysis plan will be written and signed off before analysis is undertaken. The analysis will focus on descriptive statistics and CI estimation rather than formal hypothesis testing. All analyses will be undertaken on the intention-to-treat population, with all participants included in the analysis according to their randomised allocation, and regardless of non-adherence to the intervention components or withdrawal from the trial. Final analysis will be conducted once all available outcome data are received. Outcome measures will be scored according to relevant scoring manuals. Predefined progression criteria will be used to judge the feasibility of progressing to the optimisation trial (table 5). Proof of principle will be explored via investigation of between-group change in outcomes. Point estimates and 95% CIs will be presented for the main effects and interaction effects for adherence and quality of life outcomes. Point estimates and 95% CIs for process variables will be presented for the intervention components in which a change is hypothesised. Analysis will adjust for the stratification factor.

**Table 5 T5:** Progression criteria for deciding whether or not to proceed to the optimisation trial

	Green	Amber	Red
Eligible patients consent rate	≥30%	≥10%	<10%
Component adherence			
75% of SMS messages received with no opt out	≥50%	≥20%	<20%
Read ‘at least some’ of the information leaflet	≥50%	≥20%	<20%
Completed 2/4 ACT modules	≥50%	≥20%	<20%
Registered and logged onto website at least once	≥50%	≥20%	<20%
Availability of adherence measures with ≥75% complete data	≥2	≥1	0

Green (go): optimisation phase is feasible with no changes to design or procedures; amber (modify): optimisation phase is feasible following minor enhancement of procedures; red (stop): optimisation phase is not feasible.

ACT, Acceptance and Commitment Therapy; SMS, short message service.

A rapid evaluation approach will be used for the qualitative interviews.^97^ Rapid Research Evaluation and Appraisal Lab (RREAL) sheets, which are summary tables collected after an interview, will be created for each individual participant and collated into higher level summary sheets.^98^ Regular team meetings will discuss emerging findings, changes to the interview schedule and data saturation. The interviews will be recorded. The RREAL sheets will be used to guide analysis, and illustrative quotes used to support themes.

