Authorised individuals at NHS sites will be given access to the Clinical Trials Research Unit (CTRU) online database and will enter site and participant details, and confirm eligibility and informed consent. After recording consent, the RN will register the participant and a link to the baseline questionnaire will be sent automatically from the CTRU. Once completed, the RN will notify the CTRU that a participant can be randomised, and an authorised member of the CTRU will perform the randomisation. Participants will be randomised to one of eight experimental conditions (table 1). Stratified permuted block randomisation will ensure experimental conditions are well balanced for the recruitment route. Participants, therapists, RNs, participants’ GPs and CTRU staff (including the Chief Investigator) will not be blinded to the randomised allocation. The RN will notify participants of their allocation.

We will ask participants to complete electronic follow-up questionnaires at 2 and 4 months postrandomisation. Non-responders will receive telephone, email and/or SMS message reminders.

Patients may withdraw from the SMS and ACT intervention components, completing the questionnaires, or from the collection of data from NHS Digital and data processing. The local principal investigator may decide a participant should be withdrawn if they have become unsuitable for the trial. The analysis will use data collected up to the date of withdrawal of consent.

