Acceptability questionnaire	Questionnaire	Self-completion				X	
Questionnaire return	Online system	Delegate		X	X	X	
Trial withdrawals	CRF	Delegate	X (collected throughout)				
Study Participant Feedback Questionnaire (SPFQ)	Questionnaire	Self-completion		X	X	X	
Fidelity of receipt and enactment of intervention components	Semi-structured interview	Interview				X	X
Barriers and facilitators to trial participation and response rates	Semi-structured interview	Interview					X
Barriers and facilitators to recruitment	Questionnaire	Research nurse self-completion					X
Research nurse demographics	CRF	Research nurse		X			
UK Cancer Costs Questionnaire	Questionnaire	Self-completion			X	X	
Questionnaire reminder preference	Questionnaire	Self-completion				X	

ACT, Acceptance and Commitment Therapy; BMQ-AET, Beliefs about Medication Questionnaire - Adjuvant Endocrine Therapy; CRF, Case Report Form; CTRU, Clinical Trials Research Unit; DASS-21, Depression Anxiety Stress Scales; DOSE-nonadherence, Domains of Subjective Extent of non-adherence; EORTC QLQ, European Organisation for Research and Treatment of Cancer Quality of Life Questionnaire; EQ-5D-5L, EuroQol 5 domains 5 levels; MMAS, Morisky Medication Adherence Scale; MPFI, Multi-Dimensional Psychological Flexibility Inventory; NHS, National Health Service; PI, Principal Investigator; PSSRU, Personal Social Sciences Research Unit; QoL, Quality of Life; RN, Research nurse; SMS, short message service; SRBAI, Self-Report Behavioural Automaticity Index.

**Table 4 T4:** Summary of ACT therapist assessments

Assessment	Source	Method of completion	Post-therapist training	Pretrial delivery	First session	Second session	Third session	Fourth session	Fifth session	End of trial
Consent	Consent form	Therapist	X							
Demographics	CRF	Therapist	X							
ACT-FM Competency Assessment (Therapist stance subscale)	Questionnaire	ACT trainer			X					
Number of booster training sessions required	Questionnaire	ACT trainer		X (collected throughout)						
ACT-FM therapist stance subscale	Questionnaire	Independent expert reviewer								X
Procedural Fidelity Checklist	CRF	Therapist			X	X	X	X	X	
Fidelity of training and delivery	Semi-structured interview	Interview								X

ACT, Acceptance and Commitment Therapy.

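### The Analysis section names recruitment route as the only adjustment variable and leaves between-group change undefined; adding each scale's own baseline score would narrow the exploratory intervals at almost no cost

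*Protocol article*

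**What the plan says.** The Analysis section sets the aim as estimation: "The analysis will focus on descriptive statistics and CI estimation rather than formal hypothesis testing". It then makes three statements about effects:

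- On the type of comparison, it says: "Proof of principle will be explored via investigation of between-group change in outcomes".
- On what is to be reported, it promises estimates with intervals for main and interaction effects on the adherence and quality-of-life outcomes. Process variables get the same treatment for the components expected to move them.
- On adjustment, it says: "Analysis will adjust for the stratification factor".

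The Trial processes section identifies the factor: "Stratified permuted block randomisation will ensure experimental conditions are well balanced for the recruitment route". There are three routes.

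That section also fixes when baseline is measured. After consent and registration, "a link to the baseline questionnaire will be sent automatically from the CTRU", and the participant is released for randomisation only once it is completed. Table 3 (Measures) marks MMAS-8, the DOSE extent scale, QLQ-C30, QLQ-BR45, IL133, EQ-5D-5L, MPFI, BMQ-AET, SRBAI, DASS-21 and the McGill scale at baseline, 2 months and 4 months. Not every instrument has a baseline: the "UK Cancer Costs Questionnaire" is marked at 2 and 4 months only, and the acceptability questionnaire at 4 months only.

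The Analysis section opens by deferring detail: "A detailed statistical analysis plan will be written and signed off before analysis is undertaken".

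**The concern.** The text does more than defer. It names an adjustment variable and a type of comparison, and it does not mention the baseline score of the same scale, which is usually the covariate most strongly related to the follow-up score.

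The word *change* can be read in two ways. It may mean follow-up minus baseline, or it may simply mean a difference between groups at follow-up. The two analyses have different precision, and under the usual assumptions neither is as precise as a model with the baseline score as a covariate.

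Two things are at stake, both modest. First, interval estimation is the declared focus and the sample is small, so avoidable width matters. Second, objective (iv) in the Introduction is to estimate the variability of the planned outcomes, and the Sample size section says the pilot will inform the size of the optimisation trial. If that trial adjusts for baseline, it needs the residual SD or, equivalently, the raw SD together with the baseline-to-follow-up correlation.

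**Working it through.** **Inputs from the protocol article**

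- Randomised: 80, with 10 in each of 8 conditions (Table 1; Sample size).
- Retention: 80% (Sample size).
- Each component is present in four of the eight conditions, so a main effect compares 40 with 40 at randomisation (Table 1).
- Recruitment routes: three, which take two degrees of freedom.

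**Assumed, because the documents do not give it**

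- r, the baseline-to-follow-up correlation, over the range 0.3 to 0.8. It may differ by scale and by visit.
- Equal SD at baseline and follow-up (set to 1), a linear relation, and even retention across conditions.

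**The plan's own figure.** 8 × 10 = 80, and 80 × 0.80 = 64 women at follow-up, or 32 v 32 for each main effect. The arithmetic is consistent. The plan states no SD, effect size, power or interval width, so there is no precision figure to reproduce.

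**Variance of a main effect, relative to the follow-up score alone (= 1)**

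- Change score: 2(1 − r).
- Baseline score as covariate: 1 − r².
- Saving against the change score: 1 − (1 − r²)/[2(1 − r)] = 1 − (1 + r)/2 = (1 − r)/2.
- Saving against the follow-up score alone: 1 − (1 − r²) = r².

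**95% half-width in SD units.** This is t × √(2/32) × √(relative variance), and √(2/32) = 0.25. With eight condition parameters and two for route, 64 − 10 = 54 degrees of freedom remain, or 53 once the baseline score is added. t is about 2.01 in both cases, so the lost degree of freedom is immaterial.

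| r | Change: variance | Change: half-width | Baseline covariate: variance | Baseline covariate: half-width | Saved v change | Saved v follow-up only |
|---|---|---|---|---|---|---|
| 0.3 | 1.40 | 0.59 | 0.91 | 0.48 | 35% | 9% |
| 0.5 | 1.00 | 0.50 | 0.75 | 0.43 | 25% | 25% |
| 0.7 | 0.60 | 0.39 | 0.51 | 0.36 | 15% | 49% |
| 0.8 | 0.40 | 0.32 | 0.36 | 0.30 | 10% | 64% |

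The follow-up score adjusted for route only has a half-width of 0.50 throughout, taking route as unrelated to outcome.

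**Reading the table.** The two readings of *change* pull in opposite directions. At low r a change score is the costlier choice, and at r = 0.3 it is worse than ignoring baseline (0.59 against 0.50). At high r, analysing follow-up alone is the costlier choice. They meet at r = 0.5, where either reading loses the same 25% of variance. The baseline-covariate model has the smallest half-width in every row.

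**Objective (iv).** Required sample size is proportional to the variance used. If the optimisation trial adjusts for baseline, sizing it on the raw SD overstates the relevant variance: 9%, 25% or 49% of the number so calculated is not needed at r = 0.3, 0.5 or 0.7. This is conditional, because the article does not give that trial's analysis model.

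**The case against.** The strongest answer is that the article does not state an error. A reader might infer that the analysis adjusts for route and nothing else, or that baseline scores are left out of the model. The text says neither. It names one covariate without excluding others and specifies no model, so it cannot be shown to omit a term. A reader might equally infer a change-score analysis, but the same section also uses the word loosely for an expected effect on process variables. If change from baseline is meant, baseline is already used, and the loss is that of a change score only.

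Outcome-specific covariates are routine SAP content, a SAP is announced, and the article summarises a longer protocol. The baseline covariate may already be specified there.

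The consequence is also limited. The article lists among its limitations that effectiveness will not be examined, the primary outcomes are the progression criteria, no criterion in Table 5 uses an effect estimate, and the sample of 80 does not rest on interval width. Nothing prevents the team from reporting a residual SD and a correlation from data it already holds.

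All of this stands, and it limits the point to an efficiency matter. What remains is that the published text commits to a named adjustment and an ambiguous comparison. Carried out as written, on either reading, it gives wider intervals than the same data allow.

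**Conclusion.** The point holds as a modest efficiency improvement. Recruitment route is the only adjustment variable stated, the comparison is undefined, and a pre-randomisation score exists for the eleven adherence, quality-of-life and process scales listed above. Using it would cut the variance of each main effect by 35%, 25% and 15% (change score) or 9%, 25% and 49% (follow-up only) at r = 0.3, 0.5 and 0.7. At r = 0.5 the half-width falls from about 0.50 to 0.43 SD with 64 women. These figures rest on assumed correlations, equal variances and 80% retention.

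Three stronger conclusions are not supported: that the plan rules out baseline adjustment, that every outcome has a baseline value (the cost and acceptability questionnaires do not), and that the pilot's validity, its sample size or its progression decision is affected.

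**What to change.** Replace the adjustment sentence in the Analysis section, or align it with the SAP, along these lines:

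> Each scale measured at baseline will be analysed at 2 and 4 months, adjusting for its own baseline score and recruitment route. Between-group change means the adjusted difference at that visit. The residual SD and the baseline-to-follow-up correlation will be reported alongside the raw SD, to inform the size of the optimisation trial.

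Instruments without a baseline, namely the cost and acceptability questionnaires, are outside this sentence.

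The cost is a sentence of text and about one degree of freedom per outcome, with no new data and no change to the number randomised. If the SAP already specifies the baseline covariate, only the wording of this section needs aligning.

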### Participants

Adult women using tamoxifen, raloxifene, anastrozole, letrozole or exemestane as AET for early-stage (1–3a) breast cancer are eligible (table 2).

**Table 2 T2:** Eligibility criteria for participation in the ROSETA pilot trial

Inclusion criteria	Exclusion criteria
An informed consent form (signed and dated) Capacity to provide informed consent Women with early stage (1–3a) breast cancer according to the TNM/American Joint Committee on Cancer (AJCC) staging system. *Note: Women being treated for a second primary breast cancer or a breast cancer local recurrence are eligible for the study, providing the most recent cancer is being treated with adjuvant endocrine therapy and they meet all eligibility criteria. Women with bilateral breast cancer are permitted, providing at least one breast is affected by hormone receptor-positive disease.* Aged≥18 years at time of screening for ROSETA’s pilot study Have sufficient proficiency in English to be able to adhere to all intervention components and data collection required Treated with curative intent Completed their hospital-based treatment (eg, surgery, radiotherapy and/or chemotherapy) for the current breast cancer within the last 12 months. *Note: Women are still eligible for the study if they are being treated with monoclonal antibody-based therapy such as trastuzumab, kadcyla, pertuzumab and phesgo* Currently prescribed oral adjuvant Hormone Therapy (tamoxifen, raloxifene, anastrozole, letrozole and exemestane) The participant is willing to complete the study questionnaires.* The participant is willing to be audio recorded during the therapy sessions* The participant is willing and able to attend all ACT sessions either via video conference or telephone* The participant is willing and able to complete home practice tasks* Access to a mobile phone to receive SMS messages* Willing to receive frequent SMS messages* Access to a computer or smart device that can access the internet*	Stopped taking adjuvant hormone therapy if it is clinically contraindicated according to clinical recommendation Women with metastatic breast cancer Currently or recently (last 6 months) involved in a similar research study where medication adherence is a primary outcome* Currently attending psychotherapy/psycho-oncology/psychology/counselling services, for any clinical reason* Need for treatment for a severe mental health disorder or crisis, which is likely to interfere with participation (eg, active psychosis, bipolar disorder, significant issues with addiction or self-harm or expressing active suicidal ideation with active plans and intent*) *Note: If concerned about the possible presence of risk of suicidal ideation with active plans and intent, then this can be assessed with the following questions, with patients ineligible if they answer ‘yes’ to 5c*. *Recently (in the last month):* *Have you had any thoughts about ending your life?* *(if yes) Have you thought about how you might go about it?* *(if yes) Do you intend to carry out this plan?* Patients with a scheduled date for breast reconstruction surgery that is within their intervention delivery and follow-up period. *Note: Women planning to have a breast reconstruction but who have not scheduled a date for surgery are permitted* Auditory problems that would prevent the patient from participating in a telephone or video call, or hearing audio clips*

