### Trial processes

Participants will be identified via three routes. Route 1 involves the research nurse (RN) prospectively screening patient records prior to clinic visits. Route 2 will identify patients who have self-referred to their care team to discuss problems with their medications. Route 3 involves the RN retrospectively searching patient records to identify patients who have completed hospital treatment. All patients should have completed their last hospital treatment within 12 months of randomisation.

Sites will complete a screening form for all identified patients. Anonymised data on age, ethnicity, staging, tumour type and whether a patient is randomised will be captured. Patients who are not randomised will have the reason they are ineligible or declined participation recorded.

For recruitment route 1, a member of the care team will introduce a RN to the patient, and offer the option of receiving trial documents by email. Eligible patients may consent immediately or after further consideration. In route 2, the patient’s oncologist will conduct an initial review of eligibility and, where participants are willing, provide their contact details to a RN who will telephone them and email trial documents. Interested patients contact the RN by telephone and consent is taken. For route 3, the RN will post or email the patient an invitation letter and a copy of the patient information sheet. For all routes, a RN will confirm eligibility and record consent (online supplemental appendix 4). Eligibility and consent discussions, and completion of baseline measures may take place in person or remotely.

10.1136/bmjopen-2022-069971.supp4Supplementary data

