### Measures

The primary outcomes for the study are the progression criteria (consent rate, component adherence and medication adherence measures). Secondary outcomes include quality of life, costs, psychological flexibility, beliefs about medications, habit formation, psychological distress, safety, acceptability, trial experience and fidelity. Tables 3 and 4 summarise timing of data collection for each assessment.

**Table 3 T3:** Summary of assessments

Assessment	Source	Method of completion	Timeline				
			Screening	Baseline	2 months	4 months	End of trial

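### The consent-rate progression criterion is taken among eligible patients, but eligibility includes willingness to take part, so some refusals leave the denominator and the rate is biased upward

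*Protocol article*

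**What the plan says.** The Measures section makes the progression criteria the primary outcomes: "The primary outcomes for the study are the progression criteria (consent rate, component adherence and medication adherence measures". In the Analysis section, Table 5 gives the first of them as the "Eligible patients consent rate", green at 30% or more, amber at 10% or more and red below 10%. Green means that the optimisation phase can go ahead unchanged; amber means that it is feasible after minor enhancement of procedures.

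Eligibility is set out in Table 2 (Participants). The inclusion list opens with "An informed consent form (signed and dated"). Further down come items on willingness, for example "The participant is willing to complete the study questionnaires" and "The participant is willing to be audio recorded during the therapy sessions", followed by willingness and ability to attend every ACT session, willingness and ability to do the home practice, and willingness to receive frequent texts. The table footnote says that the source for these willingness items is wholly or partly the patient's own report.

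Trial processes describes how eligibility and refusal are recorded: "For all routes, a RN will confirm eligibility and record consent", and "Patients who are not randomised will have the reason they are ineligible or declined participation recorded". The same section speaks of eligible patients who may then consent at once or later.

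**The concern.** A consent rate is meant to show how many women who could join the trial agree to do so. Reluctance to have therapy sessions, be recorded or receive frequent texts is an obvious reason for saying no to this trial. Table 2 turns each of these reasons into a failure of eligibility. The woman who gives such a reason then leaves the denominator, while everyone in the numerator stays, so the rate can only rise.

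The screening form asks why a patient was ineligible or declined, but the article gives no rule for a reason that fits both. The value of a primary outcome then depends on how each site codes the same conversation. At stake is whether the optimisation trial is judged ready to start unchanged or in need of changes to its recruitment procedures first.

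**Working it through.** **Setting the sections side by side.** Table 2 makes willingness part of eligibility. Table 5 divides by eligible patients. Trial processes separates ineligible from declined without saying where unwillingness belongs. Following Table 2 literally, unwilling means ineligible. Following the ordinary sense of declined, unwilling means eligible and not consenting. The two readings give different rates from the same women.

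**Inputs.**
- Thresholds: 30% and 10% (Table 5).
- Consenters: 80, the planned number randomised (Sample size), used as the numerator. The plan's own figure reproduces: 8 conditions × 10 = 80.
- Pool D of women approached or invited who meet every criterion apart from consent and willingness: not given in the article, so a range is assumed. No expected consent rate is stated, so there is none to reproduce.

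**Step 1, largest denominators.** Green needs 80/D ≥ 0.30, so D ≤ 80/0.30 = 266.7, that is 266. Amber needs D ≤ 80/0.10 = 800.

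**Step 2, rate when unwillingness counts as declining, and the shift needed for green.** Rate = 80/D. Refusals = D − 80. Refusals that must be classed as ineligible = D − 266, after which the rate is 80/266 = 30.1%.

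| Assumed D | Rate | Table 5 | Refusals | Must move for green | Share of refusals |
|---|---|---|---|---|---|
| 300 | 26.7% | amber | 220 | 34 | 15.5% |
| 320 | 25.0% | amber | 240 | 54 | 22.5% |
| 400 | 20.0% | amber | 320 | 134 | 41.9% |
| 600 | 13.3% | amber | 520 | 334 | 64.2% |
| 1000 | 8.0% | red | 920 | 734 | 79.8% |

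A modest share is enough when the true rate is just below 30%; a large share is needed when it is far below. Red to green would take about 80% of refusals at D = 1000. At that same D, red to amber would take 1000 − 800 = 200 of 920 refusals (21.7%).

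**Step 3, effect on the eligibility rate.** At D = 320, moving 54 women lowers the share of the pool counted as eligible from 320/320 to 266/320 = 83.1%. The product is unchanged: 83.1% × 30.1% = 25.0%. The shift is therefore visible if both rates are read together, but Table 5 sets no threshold on eligibility or on randomised over approached.

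**The case against.** The strongest reply is that the article summarises a longer protocol and defers to an analysis plan, either of which may define the denominator. That is fair as far as it goes. But the point is not only a missing definition: the published eligibility table, combined with the published criterion, gives a rule, and that rule removes refusals.

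A reader might infer that the rate is circular and must equal 100%, since a signed form is itself an inclusion item. The documents do not support this as a description of practice. Trial processes puts eligibility before consent and expects a category of women who declined, so the form is better read as a condition of entry.

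A reader might also infer that Route 3 patients who never answer the invitation fall out of the denominator. Nothing in the article says so. Sites complete a screening form for all identified patients, and non-responders could equally be counted as eligible and not consenting.

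It can further be said that the eligibility rate is also an objective, that reasons are logged, and that eligibility times consent still projects recruitment correctly under the same criteria. This stands, and it limits the damage to planning. It does not protect the Table 5 decision, which looks at the consent rate alone.

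Finally, the size is hypothetical, and amber still means feasible. Both are true. Nothing in the article shows what share of refusals would be given as unwillingness on a named activity.

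**Conclusion.** The concern holds in this form: applied as written, Table 2 takes women who refuse specified trial activities out of the denominator of a primary progression criterion, which biases the rate upward. The realistic consequence is amber read as green, with uptake unchanged: for example 25.0% becoming 30.1% if 54 of 240 refusals are moved. This rests on 80 consenters and an assumed pool of 320. The direction of the bias does not depend on those figures; its size does.

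The scope is limited. The consent rate belongs to one of three groups of primary criteria. The willingness items do not cover every component: none concerns reading the leaflet, and for the website only internet access is required. Neither the 100% reading nor a loss of Route 3 non-responders is established by the text, and red to green would need an implausibly large reclassification.

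**What to change.** In the analysis plan, before sign-off, define the denominator for the Table 5 consent criterion as patients approached or invited who are not known to fail any Table 2 criterion other than the signed consent form and the willingness items. Then:

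- Count unwillingness on any trial activity as declining. Two of the items combine willingness with ability; only the willingness part should be moved.
- Keep true exclusions as ineligibility even where they are self-reported: current psychotherapy, severe mental health crisis, recent involvement in a similar study, disabling hearing problems, no mobile phone or no internet device. Dropping every self-reported item would count these women as non-consenters and bias the rate downward.
- Apply the 30% and 10% thresholds to that rate.
- State, by recruitment route, how invited non-responders are counted.
- Report alongside it the narrower rate that follows Table 2 literally, and randomised over approached.

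The cost is a paragraph of wording and a recode of reasons that sites already record, provided those reasons are specific enough to separate unwillingness from other ineligibility. No new data are needed. The downside is a rate that may be lower and could fall from green to amber.
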